# A phase II RCT and economic analysis of three exercise delivery methods in men with prostate cancer on androgen deprivation therapy

**DOI:** 10.1186/s12885-015-1316-8

**Published:** 2015-04-25

**Keywords:** Prostate cancer, Androgen deprivation therapy, Exercise, Randomized controlled trial, Quality of life, Fatigue, Physical fitness, Cost-effectiveness, Patient adherence

## Abstract

**Background:**

Androgen deprivation therapy is commonly used to treat prostate cancer, the most common visceral cancer in men. However, various side effects often worsen physical functioning and reduce well-being among men on this treatment. Based on existing evidence, both resistance and aerobic training provide benefits for this population yet adherence rates are often low. The method of exercise delivery (supervised in-center or home-based) may be important, yet few studies have compared different models. Additionally, long-term exercise adherence is critical to achieve sustained benefits but long-term adherence data and predictors of adherence are lacking. The primary aim of this phase II, non-inferiority randomized controlled trial is to determine whether three exercise training delivery models are equivalent in terms of benefits in quality of life and physical fitness in this population. Secondary aims include examination of long-term adherence and cost-effectiveness.

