Thus, the primary aims of this phase II non-inferiority RCT are:To determine the feasibility of conducting a large multi-center non-inferiority RCT of three exercise delivery models in men with PC on ADT. Feasibility outcomes include participant recruitment, retention, adherence, outcome capture, and satisfaction;To obtain preliminary efficacy estimates for (a) group-supervised in-centre, and (b) home-based (smartphone-assisted) supported exercise programs, compared to (c) a 1:1 supervised in-center exercise program study for the clinical outcomes of QOL and physical fitness, and to select a primary outcome for a subsequent phase III trial;To examine adherence to exercise and predictors of adherence in each exercise group during the 6-month intervention and for 6 months after program completion;To determine the feasibility of conducting an economic analysis comparing exercise interventions and usual care.

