### Sample size calculation/power

Following standard guidelines for a phase II RCT [58-60], we have targeted 30 patients per arm (90 patients in total) to provide precise estimates of parameters related to the primary outcomes as well as important feasibility information that will be crucial to inform the phase III study. Assuming 10% drop-out, we will recruit 100 patients across both sites.

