### Statistical analysis

Statistical analysis focuses on feasibility outcomes and those which will inform decisions about moving forward to and planning a phase III clinical trial. Feasibility outcomes include recruitment rates, and proportions of participants retained and adherent at landmark times throughout the study, all of which will be estimated with 95% confidence intervals. Additionally tallies are kept on reasons for not participating. Each participant also completes an exit interview and satisfaction survey which will be analyzed for participant satisfaction within the study and cost effectiveness analysis.

Adherence is assessed through the two different binary definitions given previously, based on steps or hours of exercise. We estimate proportions adhering to exercise in each three-month period and use generalized estimating equation logistic regression models to compare adherence between groups and assess predictors of adherence over the course of the study. Predictors include sociodemographic (e.g. age, education), clinical (disease stage), baseline fitness, and ecological variables (NEWS, etc.).

Quality of Life (FACT-G and FACT-P), musculoskeletal fitness, and aerobic fitness are efficacy outcomes that are analyzed using linear mixed effects model with subject-specific random effects and group-by-time interactions. The analysis will not focus on differences between groups, but, to assist with phase III trial design, estimation of measures of within and between-person variance.

As previously mentioned, there is no formal cost-effectiveness analysis, however data obtained (diary and EQ-5D completion and participant acceptance) is used to help develop this outcome for the phase III study. Descriptive estimates of costs by category and per intervention arm as well as per site (Toronto, Calgary) will be calculated.

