The current study is designed to address important limitations in prior studies and advance the science of exercise delivery for men on ADT. First, this study is directly comparing the three main exercise delivery models to identify whether less resource-intense approaches are as efficacious as the reference standard of supervised personal training. Second, adherence will be carefully studied during and, more importantly, after the formal six-month intervention period. Moreover, insights will be gained into enabling factors and barriers to exercise adherence. Third, we will formally begin to evaluate the cost effectiveness of each exercise delivery model; such information should ultimately inform health policy. Additional innovations include structured exercise tapering (to facilitate independent exercise), introduction of a smartphone app and health coach support to enhance home-based exercising, and other features.

The evidence-based knowledge gained with this research will provide an understanding of the best (clinically effective, high adherence, cost effective) exercise program for this population and will help strengthen research in this field. Although the results from the phase II trial will not be definitive, this step is foundational and the knowledge that will be generated will be incorporated into the design and execution of a multi-center phase III RCT.

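### The abstract's primary aim and the non-inferiority label do not match the body's aims, sample-size basis or analysis emphasis

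*Protocol article*

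**What the plan says.** **Abstract, Background.** One primary aim is given: "The primary aim of this phase II, non-inferiority randomized controlled trial is to" then "determine whether three exercise training delivery models are equivalent in terms of benefits in quality of life and physical fitness in this population". Long-term adherence and cost-effectiveness are named as secondary.

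**Background, list of aims.** The non-inferiority label is kept, but there are four primary aims. The first is "To determine the feasibility of conducting a large multi-center non-inferiority RCT of three exercise delivery models in men with PC on ADT". The second is "To obtain preliminary efficacy estimates for (a) group-supervised in-centre, and (b) home-based (smartphone-assisted) supported exercise programs, compared to (c) a 1:1 supervised in-center exercise program", together with the intention "to select a primary outcome for a subsequent phase III trial". The third is adherence and its predictors. The fourth is whether an economic analysis is feasible.

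**Sample size calculation/power.** The basis is phase II guidance: "we have targeted 30 patients per arm (90 patients in total) to provide precise estimates of parameters". No margin, alpha or power enters.

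**Statistical analysis.** QOL and fitness are fitted with a linear mixed model that has random subject effects and an arm-by-time interaction. The text then says "The analysis will not focus on differences between groups" and directs attention to variance components for planning phase III.

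**Criteria to move forward to phase III RCT.** An arm shown to be inferior to the other two is dropped, and QOL and fitness results are among the permitted grounds.

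**Discussion.** The study compares the models "to identify whether less resource-intense approaches are as efficacious as the reference standard of supervised personal training". The section's closing paragraph concedes that the phase II results will fall short of being definitive.

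**The concern.** A primary aim tells the reader what verdict to expect. The abstract promises one on equivalence and the label promises one on non-inferiority. Either verdict needs a margin, a confidence-limit rule set against it, and a sample size derived from it. The body reports a sample size reached another way and an analysis pointed elsewhere.

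Two things are at stake. First, someone who takes the aim from the abstract may read an inconclusive comparison as support for equivalence. That reading would favour the group and home programmes, which the Background section expects to bring service-delivery and economic gains if they perform similarly. Second, the analysis section plays down the same between-arm differences that Aim 2, the arm-dropping rule and the Discussion sentence use.

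**Working it through.** **1. The stated sample size.** 30 × 3 = 90, and 90 / (1 − 0.10) = 100. The recruitment target is reproduced. The 30 per arm has no alpha, power, effect or margin behind it to recompute.

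**2. The passages side by side.**

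| Item | Abstract | Body |
|---|---|---|
| Primary aim | Equivalence on QOL and fitness | Feasibility; preliminary estimates; adherence; economic feasibility |
| Adherence | Secondary | Third primary aim |
| Basis for 30 per arm | Not given | Precision and feasibility |
| Efficacy analysis | Implied verdict between arms | Emphasis on variance components |
| Users of between-arm differences | The primary aim | Aim 2, arm-dropping rule, Discussion |

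The outcome for phase III is also still to be chosen under Aim 2, although Table 1 marks FACT-G as primary.

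**3. What 30 per arm could show.** The article states no margin, SD, alpha or power. The following are assumptions: one-sided alpha 0.025, true difference 0, normal approximation, margins in SD units, and baseline adjustment that multiplies the standard error by √(1 − ρ²), where ρ is the baseline-to-follow-up correlation.

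- Unadjusted standard error of a pairwise difference: √(2/30) = 0.258 SD.
- 95% CI half-width: 1.96 × 0.258 = 0.51 SD.
- Smallest margin with 80% power: (1.96 + 0.8416) × 0.258 × √(1 − ρ²).
- Power at margin m: Φ(m / [0.258 × √(1 − ρ²)] − 1.96).

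| ρ | Half-width (SD) | Margin for 80% power (SD) | Power at 0.5 SD | Power at 0.3 SD |
|---|---|---|---|---|
| 0 | 0.51 | 0.72 | 49% | 21% |
| 0.5 | 0.44 | 0.63 | 61% | 27% |
| 0.7 | 0.36 | 0.52 | 77% | 37% |
| 0.8 | 0.30 | 0.43 | 90% | 49% |

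The abstract's word is equivalence, which is two-sided. With two one-sided tests at 0.05 and no adjustment, 80% power needs a margin of (1.645 + 1.2816) × 0.258 = 0.76 SD.

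**4. At the lowest retention accepted.** The progression criteria allow 70% retention: 0.70 × 100 / 3 ≈ 23 per arm. Unadjusted, the half-width is 1.96 × √(2/23) = 0.58 SD and the margin for 80% power is 2.8016 × √(2/23) = 0.83 SD.

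**The case against.** The strongest reply is that the body already behaves as a phase II study should. Its aims speak of feasibility and preliminary estimates, the sample size is justified accordingly, the analysis serves phase III planning, and the Discussion says the results will not settle the matter. Declining to focus on group differences is itself some protection against over-reading. All of this stands, and it limits the harm. It does not correct the abstract's aim or the label, which the body repeats, and the Discussion's caveat sits beside a sentence that claims more.

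Three stronger readings are tempting, and the document supports none of them.

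- *Aim 2 loses its output.* It does not. The mixed model with arm-by-time terms can yield both contrasts with intervals, and not focusing on differences is not the same as withholding them. Which contrasts are tabulated, and at which visit, may properly be left to the analysis plan.
- *The design could never support non-inferiority.* That is too absolute. With a baseline correlation of 0.8, a 0.5 SD margin would have about 90% power for a single comparison. A margin may also sit in a document not shown. Even so, the sample-size section gives a different basis for 30 per arm, and the analysis section points away from the comparison.
- *The trial is too small.* For feasibility and estimation, nothing here shows that.

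**Conclusion.** The point holds as an inconsistency in the article's own text, and it should be fixed. The abstract's aim and the non-inferiority label describe a property that the trial is neither sized nor primarily analysed to have. Adherence is secondary in one place and primary in another. The stated analysis emphasis is at odds with three uses of between-arm differences elsewhere in the article.

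This conclusion rests on the wording alone. The power figures only illustrate it: they depend on an assumed margin, alpha and baseline correlation, and at a 0.5 SD margin they run from 49% to 90%. A reader might infer a failed design or a missing analysis. The evidence goes no further than a misstated aim and label and a misdirected emphasis.

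**What to change.** Keep the sample size, data collection and model. Change the following.

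1. **Abstract and Background.** Describe the study as a randomised phase II feasibility and estimation trial that prepares a phase III non-inferiority trial. Bring the abstract's aim into line with the Background list, and give adherence the same status in both places.
2. **Interpretation.** State that neither equivalence nor non-inferiority will be concluded from this trial, and soften the Discussion sentence to agree.
3. **Statistical analysis.** State that the group minus 1:1 and home minus 1:1 differences will be reported from the planned mixed model with 95% CIs, as preliminary estimates. Six months, the end of the intervention, is one natural time point; the article does not fix one.
4. **Criteria to move forward to phase III RCT.** Reconcile the wording that an arm proves inferior on QOL or fitness with an analysis that only estimates.

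The cost is rewording plus two contrasts from a model already planned. The stated claim becomes less favourable, which is the one real downside.

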**Design:**

Men diagnosed with prostate cancer, starting or continuing on androgen deprivation therapy for at least 6 months, fluent in English, and living close to one of two experienced Canadian study centers are eligible. Participants complete five assessments over one year, including a fitness assessment and self-report questionnaires. Socio-demographic and clinical data collection occur at baseline, bone mineral density testing at two time points, and blood work is performed at three time points. Participants are randomized in a 1:1:1 fashion to supervised personal training, supervised group training, or home-based smartphone- and health coach-supported training. Each participant receives a detailed exercise manual, including illustrations of exercises and safety precautions. Participants are asked to complete 4 to 5 exercise sessions per week, incorporating aerobic, resistance and flexibility training. Participant intensity levels will be monitored. The intervention duration is 6 months, with 6 months additional follow-up. Outcomes include: body composition, fitness testing, quality of life and fatigue, biological outcomes, and program adherence. Cost information will be obtained using patient diary-based self-report.

**Discussion:**

The goals of this study are to gain a better understanding of health benefits and costs associated with commonly used yet currently not compared exercise delivery models as well as an increased understanding of adherence to exercise.

**Trial registration:**

The trial has been registered at clinicaltrials.gov (Registration # NCT02046837), registered January 20^th^, 2014.

## Background

Prostate Cancer (PC) is the leading cancer diagnosed in North American men [1,2]. With improvements in early diagnosis and treatment, survival has been steadily increasing for this population [2]. One common treatment for men diagnosed with PC is androgen deprivation therapy (ADT), which is estimated to be used in 45% of men with PC [3,4]. Common side effects from ADT are fatigue, decreased muscle strength and cardiorespiratory function, loss of sexual functioning, mood changes, changes in body composition and negative effects on health-related quality of life (QOL) [5-8]. These changes often lead to a decrease in overall physical functioning and individual well-being [6,9]. Modifiable factors that can limit the burden of ADT need to be identified.

Exercise in the form of both resistance and aerobic training provide benefits for individuals with PC on ADT. In a randomized controlled trial (RCT), Segal et al. [10] found improvements in fatigue in the exercise group compared to a worsening of fatigue in the control group. Improvements in QOL were also noted following this in-center, structured exercise program [10]. Galvao et al. [11] found improvements in muscle strength following a 20-week resistance and endurance training program [11]. Improvements in 6-minute walk tests, stair climbing and chair rise fitness measures were also observed. In another study, Galvao et al. found significant improvements in the general health and physical health composite scores on the Medical Outcomes Study 36-item questionnaire (SF-36) for participants who completed a 12-week aerobic and resistance exercise program, compared to usual care [12].

These trials and others have been included in multiple systematic reviews of exercise interventions for individuals on ADT for PC. These reviews have found that, generally, exercise is safe and feasible, and exercise interventions are associated with multiple benefits for this population [9,13-16]. For example, Baumann et al. concluded that exercise interventions led to improvements in fatigue levels, muscular strength, flexibility, aerobic fitness, QOL, and well-being [9]. Santa Mina et al.’s review also found similar results regarding physical functioning and QOL outcomes with the additional finding that exercise program supervision by a certified professional was an important factor in achieving greater health benefits [14]. Altogether, findings from these reviews provide strong evidence of exercise benefits for patients on ADT.

Of interest, Thorsen et al. noted that in two of the studies reviewed, older age was associated with lower levels of participation intention [13]. This may be particularly important since PC is predominantly an older person’s disease, and aging itself is associated with multiple functional declines and sarcopenia [17].

While the most consistent benefits of exercise interventions in men on ADT have been seen with 1:1 supervised programs [15], few studies have directly compared exercise delivery methods. The systematic review by Keogh et al. noted significantly greater improvements in outcomes (physical functioning and QOL) for individuals in group-based supervised training vs. home-based training [15]. However, three important things should be noted. First, the noted improvement with group-based training compared to home-based training was based on indirect study comparisons. Second, home-based training provided significant pre-post increases in aerobic endurance and reduced fatigue. Third, only one RCT has directly compared multiple exercise delivery methods, comparing only 1:1 and group supervised training, but with a small sample size and without a home-based arm [18]. Because in-center, supervised, exercise programs are resource-intensive (and largely inaccessible), the demonstration of similar efficacy in home-based programs to these supervised programs would have important health service delivery implications and economic benefits and may help expand exercise delivery options for men on ADT.

It is also clear that the benefits obtained from an exercise program are maintained only as long as the exercise is maintained; therefore ensuring long term adherence to exercise programming has significant health implications. In RCTs of exercise in PC, adherence responses to exercise interventions are moderate to high but vary by protocol design. Supervised exercise intervention adherence ranged from 79% to 95% (as assessed by attendance at scheduled sessions) in three studies [10,19,20], whereas in a study of group-based training the attendance-based adherence was 94% [11,12]. In three home-based studies, the adherence ranged from 77% to 100% (assessed by way of patient reporting, booster session attendance or weekly group session attendance) [21-23]. In spite of a moderate to high level of adherence for exercise intervention across multiple delivery approaches, only Culos-Reed et al. [21] directly measured changes in activity levels (decreased in strenuous physical activity, however mild and moderate physical activity stayed relatively the same) from post-intervention to subsequent follow-up assessment. Additionally, follow-up assessments of fitness outcomes following the post intervention assessment [20-23] are rarely reported. However, when reported longer-term benefits vary, such that there is evidence of maintenance of intervention-based improvements at 6 months follow up in one study [20] whereas no differences in fatigue levels were found from baseline to the end of a 4-week intervention and again 4 weeks later, between the control and exercise groups [23].Follow-up data post-intervention were not obtained or reported in four of the above studies [10,12,19,22].

Even though multiple rigorous studies have demonstrated improvements in several health outcomes with an exercise intervention, exercise in the oncology setting remains unfunded in most countries by health insurance programs (public and private) and organizations. This contrasts sharply with cardiovascular rehabilitation, which is publicly funded in many jurisdictions, in part due to more advanced, robust evidence demonstrating cost-effectiveness. Indeed, in today’s fiscally strained funding environment, there is an increasing emphasis on demonstrating value (or return) on investment. Demonstration of the cost-effectiveness of exercise programs for men on ADT could lead to larger scale implementation of these programs.

Thus, the primary aims of this phase II non-inferiority RCT are:To determine the feasibility of conducting a large multi-center non-inferiority RCT of three exercise delivery models in men with PC on ADT. Feasibility outcomes include participant recruitment, retention, adherence, outcome capture, and satisfaction;To obtain preliminary efficacy estimates for (a) group-supervised in-centre, and (b) home-based (smartphone-assisted) supported exercise programs, compared to (c) a 1:1 supervised in-center exercise program study for the clinical outcomes of QOL and physical fitness, and to select a primary outcome for a subsequent phase III trial;To examine adherence to exercise and predictors of adherence in each exercise group during the 6-month intervention and for 6 months after program completion;To determine the feasibility of conducting an economic analysis comparing exercise interventions and usual care.

## Methods

This trial is taking place at two experienced academic tertiary care Canadian centers – the Princess Margaret Cancer Centre (Toronto, Ontario), and the Tom Baker Cancer Centre, (Calgary, Alberta). Ethics approval has been obtained at both institutions. All study participants provide written informed consent prior to study enrolment. The trial has been registered at clinicaltrials.gov (Registration # NCT02046837).

### Study population/participants

Men diagnosed with histologically confirmed PC of any stage, starting or continuing on ADT for at least 6 months (or who remain biochemically castrate after stopping ADT), able to speak, read and write in English, and living in close proximity to either study center are eligible for the study. Each potential participant is screened with the Physical Activity Readiness questionnaire (PAR-Q+ or PARmed-X) [24] and/or receives physician approval. If an individual already meets the American College of Sports Medicine (ACSM) guidelines for moderate to vigorous physical activity (MVPA) or has a condition that would interfere with his ability to participate (e.g. severe arthritis limiting ambulation, major neuropsychiatric abnormality, severe visual/hearing loss, poorly controlled pain), he is excluded from the study.

